| ART                     | Antiretroviral therapy                                                                                                                                                                                                                                 |
| ARV                     | Antiretroviral                                                                                                                                                                                                                                         |
| BARDA                   | Biomedical Advanced Research & Development Authority, DHHS                                                                                                                                                                                             |
| CBC                     | Complete blood count                                                                                                                                                                                                                                   |
| CDC                     | Centers for Disease Control and Prevention                                                                                                                                                                                                             |
| CFR                     | Code of Federal Regulations                                                                                                                                                                                                                            |
| CIN                     | Cervical Intraepithelial Neoplasia                                                                                                                                                                                                                     |
| CMI                     | Cell-Mediated Immunity                                                                                                                                                                                                                                 |
| CRF                     | Case Report Form                                                                                                                                                                                                                                       |
| CRPMC                   | Clinical Research Products Management Center                                                                                                                                                                                                           |
| CTL                     | Cytotoxic T Lymphocytes                                                                                                                                                                                                                                |
| DAIDS                   | Division of AIDS                                                                                                                                                                                                                                       |
| DHHS                    | Department of Health and Human Services                                                                                                                                                                                                                |
| DMC                     | Data Management Center                                                                                                                                                                                                                                 |
| DTR                     | Deep Tendon Reflex                                                                                                                                                                                                                                     |
| DMID                    | Division of Microbiology and Infectious Diseases                                                                                                                                                                                                       |
| EAE                     | Expedited Adverse Event                                                                                                                                                                                                                                |
| eCRF                    | Electronic Case Report Form                                                                                                                                                                                                                            |
| Evaluable               | Evaluable subjects are defined as having received two doses of Influenza A (H1N1) 2009 Monovalent Vaccine 21-28 days apart and had all HAI samples for collected up to and including Day 10 post Dose #2 within the protocol specified windows. |
| FDA                     | Food and Drug Administration                                                                                                                                                                                                                           |
| GBS                     | Guillain-Barré Syndrome                                                                                                                                                                                                                                |
| GCP                     | Good Clinical Practice                                                                                                                                                                                                                                 |
| GMT                     | Geometric Mean Titer                                                                                                                                                                                                                                   |
| H1N1                    | 2009 Pandemic influenza A virus (swine flu)                                                                                                                                                                                                            |
| HAART                   | Highly Active Antiretroviral Therapy                                                                                                                                                                                                                   |
| HA                      | Hemagglutinin                                                                                                                                                                                                                                          |
| HAI                     | Hemagglutination Inhibition                                                                                                                                                                                                                            |
| HCG                     | Human Chorionic Gonadatropin                                                                                                                                                                                                                           |

|                     |                                                                                     |
|---------------------|-------------------------------------------------------------------------------------|
| HBV                 | Hepatitis B Virus                                                                   |
| ICH                 | International Conference on Harmonization                                           |
| IEC                 | Independent or Institutional Ethics Committee                                       |
| ILI                 | Influenza-like-illness                                                              |
| IMPAACT             | International Maternal Pediatric Adolescent AIDS Clinical Trials Group              |
| IND                 | Investigational New Drug Application                                                |
| IRB                 | Institutional Review Board                                                          |
| ISM                 | Independent Safety Monitor                                                          |
| LAR                 | Legally Authorized Representative                                                   |
| MCG                 | Microgram                                                                           |
| MedDRA ® | Medical Dictionary for Regulatory Activities                                        |
| MN                  | Microneutralization Assay                                                           |
| N                   | Number (typically refers to subjects)                                               |
| NCI                 | National Cancer Institute                                                           |
| NIAID               | National Institute of Allergy and Infectious Diseases                               |
| NICHD               | The Eunice Kennedy Shriver National Institute of Child Health and Human Development |
| NIH                 | National Institutes of Health                                                       |
| NICU                | Neonatal Intensive Care Unit                                                        |
| NP                  | Naso-pharyngeal swabs                                                               |
| Nt                  | Neutralizing                                                                        |
| OHRP                | Office for Human Research Protections, DHHS                                         |
| PI                  | Principal Investigator                                                              |
| QA                  | Quality Assurance                                                                   |
| QC                  | Quality Control                                                                     |
| RT-PCR              | Reverse Transcriptase Polymerase Chain Reaction                                     |
| SAE                 | Serious Adverse Event/Serious Adverse Experience                                    |
| SDMC                | Statistical and Data Management Center                                              |
| SMC                 | Safety Monitoring Committee                                                         |
| TIV                 | Trivalent Influenza Vaccine                                                         |
| US                  | United States                                                                       |

## SUMMARY OF CHANGES

All changes in this version appear in boldface type. Editorial changes including corrections of typographical errors and other changes required to update information that does not affect regulatory issues or patient consent may also be included. These changes contain all the information contained in Letter of Amendment #1, dated 10/13/09:

1. The Influenza A (H1N1) 2009 Monovalent Vaccine manufactured by Novartis has been approved by the FDA. All references to the study product have been modified to indicate that the study vaccine is a licensed product and is no longer considered as investigational.
2. The vaccine is now referred to as “Influenza A (H1N1) 2009 Monovalent Vaccine” throughout the protocol. The virus is now referred to as “2009 H1N1 Influenza A virus” throughout the protocol. Similarly, all references to ‘S-OIV’ or ‘swine-origin’ have been removed.
3. The Table of Contents has been updated.
4. Schema and Section 2.2 – Secondary Objectives. An additional secondary objective has been added: “To explore factors related to HIV and its treatment that might affect the responses to H1N1 vaccinations.”
5. Section 4.2 – Exclusion Criteria; Informed Consent: The Influenza A (H1N1) 2009 Monovalent Vaccine (Novartis) does not contain any of the following allergens: Gelatin, formaldehyde, octoxinol or chicken protein, but does contain neomycin and polymyxin. Therefore, exclusion criterion 4.21 has been updated to: “Has a known allergy to eggs, egg products, neomycin or polymyxin.”
6. Section 4.23 – Exclusion Criteria: This is has been expanded to include a definition of H1N1 infection, and as such now reads: “Has a history of probable or proven pandemic 2009 H1N1 Influenza A infection prior to study entry, as defined as “Symptoms of influenza-like illness as well as a proven history, by RT-PCR, of novel influenza H1N1 infection, or, has positive influenza diagnostic testing since June 2009 (specificity to H1N1 not required) prior to study entry.”
7. Section 4.7: Enrollment procedures have been updated.
8. Section 5.12; Needle Length Chart: It is recommended that all subjects in P1088 should have study vaccine administered in the deltoid muscle. Vaccinations with study vaccine that are to be administered in the lateral thigh should follow the instructions in the package insert.
9. Section 6.1 – Toxicity Management: The first bullet has been revised to read: “ALL grades of adverse events, whether or not associated with study vaccine, should be recorded on the appropriate CRF and will be assessed in the safety outcomes.”

10. **Section 6.2 and 6.5 – Subject Management:** The following text has been added: “For this protocol, the following definition of H1N1 infection will be used: “Symptoms of influenza-like illness as well as a proven history, by RT-PCR, of novel influenza H1N1 infection, or, has positive influenza diagnostic testing since June 2009 (specificity to H1N1 not required) prior to study entry.”

If a subject experiences documented H1N1 infection, as defined in Section 4.23, between Step I and Step II of the protocol, the subject should NOT receive the second dose of vaccine but should continue to be seen at the scheduled study visits, and have blood collected, as per the Schedule of Evaluations.”

11. **Section 8.5 – Study Safety Monitoring:** The following text has been added: “For safety monitoring, a vaccine related SAE is an SAE that is judged to be “definitely”, “probably” or “possibly related” to study vaccine.
12. **Appendix III – Informed Consent:** The date of the Sample Informed Consent should read: Version 2.0 dated April 23 2010.
13. **WHY IS THIS STUDY BEING DONE? (IC page 1/10)**  
Text has been modified to read: “H1N1 virus, historically known as ‘swine flu virus’, is a new strain of influenza (flu) virus that causes illness in people.”
14. **WHY IS THIS STUDY BEING DONE? (IC page 1/10)**  
Text has been modified to read: “The purpose of this research study is to determine if this vaccine which has been licensed by the United States Food and Drug Administration (FDA) is safe and will help the body’s normal defenses against the effects of H1N1 influenza in HIV-infected children and youth. The licensed vaccine to be used in this study may not prevent influenza virus infection, but may prevent severe disease and possibly death which has been seen with this H1N1 influenza virus in children.”
15. **WHY IS THIS STUDY BEING DONE? (IC page 2/10)**  
Text has been modified to read: “This vaccine contains a trace amount of thimerosal (mercury).”
16. **WHY IS THIS STUDY BEING DONE? (IC page 2/10)**  
Text has been modified to read: “The vaccine is made with products from eggs.”
17. **WHY IS THIS STUDY BEING DONE? (IC page 2/10)**  
Text has been modified to read: “If you are allergic to egg protein (eggs or egg products), you would not be able to receive this vaccine.”
18. **WHY IS THIS STUDY BEING DONE? (IC page 2/10)**  
The following text has been removed:  
“Also, if you choose not to eat pork for religious reasons, you may want to consult your religious authority regarding getting a vaccine that contains products derived from pigs.”

**19. WHAT ARE THE RISKS OF THE STUDY? (IC Page 5/10)**

The following text has been added:

“The dose of study drug is higher than the recommended dose for healthy children because children with HIV infection may not respond as well as healthy children to the lower dose of vaccine.”

**20. WHAT ARE THE RISKS OF THE STUDY? (IC Page 5/10)**

Symptoms of vaccine related reactions should be modified to read:

- skin rash (hives)
- fever
- nausea
- vomiting
- diarrhea
- abdominal pain
- cough
- sore throat
- achiness
- feeling tired (fatigue)
- general feeling of illness
- myalgia (muscle aches)

Serious Vaccine Related Reactions:

- Difficulty breathing
- Sweating
- Fast pulse
- Swelling around the mouth, throat or eyes

**21. After you have received the vaccine (IC Page 6/10)**

“Myalgia (muscle aches)” has been added to the list of vaccine-related reactions.

**22. WHAT OTHER CHOICES DO I HAVE BESIDES THIS STUDY?**

(IC page 8/10)

Text has been modified to read:

“Alternatives to your participation in this study include receiving from your health care provider the seasonal flu vaccine and Influenza A (H1N1) 2009 Monovalent Vaccine. Alternatively, you may choose not to receive any vaccine.”

**23. WHAT ARE THE RISKS OF THE STUDY? (IC page 5/10)**

Text has been modified to read:

“Life-threatening allergic reactions to vaccines are very rare. If they do occur, it is usually within a few minutes to a few hours after the vaccination.”

## SCHEMA

A Phase II Study to Assess the Safety and Immunogenicity of an Inactivated  
**Influenza A (H1N1) 2009 Monovalent Vaccine** in HIV-1  
Perinatally Infected Children and Youth

### DESIGN:

Multi-center, Phase II, open label study  
STEP I: Dose #1 of study vaccine  
STEP II: Dose #2 of study vaccine

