## 8.0 STATISTICAL CONSIDERATIONS

### 8.1 General Design Issues

This is a Phase II study in children and youth  $\geq 4$  years to  $< 25$  years old who were infected with HIV-1 via perinatal transmission. This study is designed to investigate the safety, reactogenicity, and immunogenicity of a two dose regimen of Novartis **Influenza A (H1N1) 2009 monovalent vaccine**.

The sample will be stratified into 3 age strata, which may differ with respect to immune response. Moreover, factors such as immune status at the time of first immunization and differences in background exposure to the virus across sites participating in the study

may have an impact on response to the vaccine. The study will not have an adequate sample size to provide precise estimates of immune response and adverse events rates for all subgroups which may exhibit differing results. Section 8.6 presents confidence intervals around potential subgroups of various sizes with a range of potential results to provide an indication of the precision with which these rates can be estimated.

The study will be monitored intensely by the protocol team, which will review data every other week while subjects are accruing and the vaccine is being administered and at least once a month after the last dose of study vaccine has been administered (See Section 8.5). A Safety Monitoring Committee (SMC) will be convened by IMPAACT to review safety information gathered from all study participants.

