### 8.3 Randomization and Stratification

There will be no randomization. Subjects will be stratified by age (at least 40 subjects per group):

- Group 1:  $\geq 4$  years to  $< 9$  years
- Group 2:  $\geq 9$  years to  $< 18$  years
- Group 3:  $\geq 18$  years to  $< 25$  years

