### 8.4 Sample Size and Accrual

Approximately 140 children and youth, aged  $\geq 4$  years to 25 years old, who were infected with HIV-1 via perinatal transmission will be enrolled into this study. We will enroll at least 40 subjects each from three different age groups: age  $\geq 4$  years to  $< 9$  years of age,  $\geq 9$  years to  $< 18$  years of age and  $\geq 18$  to  $< 25$  years of age. This sample size is expected to yield at least 120 evaluable\* subjects, which will provide reasonably precise estimates of rates of adverse events and immunogenic response. Evaluable subjects are defined as having received two doses of Novartis **Influenza A (H1N1) 2009 monovalent vaccine** 21-28 days apart and had all HAI samples for collected up to and including Day 10 post second dose within the protocol specified windows.

Accrual is anticipated to be 4-6 weeks.

\*Evaluable subjects are defined as having received two doses of Novartis **Influenza A (H1N1) 2009 monovalent vaccine** 21-28 days apart and had all HAI samples for collected up to and including Day 10 post Dose #2 within the protocol specified windows.

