#### 8.612 Immunogenicity

The proportion of subjects meeting the criteria for immunologic response following the first and second vaccine doses will be presented. The precision with which this sample result estimates the rate of immunologic response rates in the population represented by the study sample will be reported in terms of 90% CIs around the sample proportions. This will provide 95% confidence that the rate of

immune response is not less than the lower limit of the proportion of study subjects meeting immune response criteria.

Table 3 illustrates the confidence intervals for a range of hypothetical proportions of immunologic response. This table shows (e.g.) that a sample finding of 90 responders in the total sample of 120 subjects (75%) would provide 95% confidence that the rate in the population from which the sample was drawn was no lower than 68%. If a subsample of 20 subjects exhibited a 75% response rate, this would provide 95% confidence that the population rate was no lower than 54%.

**Table 3: Exact 90% Confidence Intervals around Potential Proportions of Subjects Meeting Immunologic Response Criteria (Total Sample and Selected Subsample Sizes)**

| N   | Sample rate | Lower Limit | Upper Limit |
|-----|-------------|-------------|-------------|
| 120 | 25%         | 19%         | 32%         |
|     | 50%         | 42%         | 58%         |
|     | 75%         | 68%         | 81%         |
|     | 90%         | 84%         | 94%         |
|     | 95%         | 90%         | 98%         |
| 40  | 25%         | 14%         | 39%         |
|     | 50%         | 36%         | 64%         |
|     | 75%         | 61%         | 86%         |
|     | 90%         | 79%         | 97%         |
|     | 95%         | 85%         | 99%         |
| 20  | 25%         | 10%         | 46%         |
|     | 50%         | 30%         | 70%         |
|     | 75%         | 54%         | 90%         |
|     | 90%         | 72%         | 98%         |
|     | 95%         | 78%         | 99.7%       |

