## 8.62 Key Secondary Analyses

Prediction of immune response will be addressed in secondary analyses. Since this is a new vaccine about which there is considerable uncertainty with respect to the distribution of antibody titers which it may elicit, alternative outcome variables will be explored. These include:

- 1) The log (10) HAI titer,
- 2) HAI titer >10, considered indicative of an immune response; and
- 3) HAI titer >40, which is considered to be likely to be protective.

The distribution of log (10) HAI titer will be examined to determine whether it satisfies the normality assumption required for linear regression analysis. If this is not true, then this method will be not be used. Since the other potential outcome

variables listed above are categorical, the method of analysis for those outcome variables will be logistic regression.

Factors predicting immune response will be examined on data collected after the first vaccination and, again, after the second. A primary predictor will be the age stratification factor. If immune response were to vary significantly across age strata, this would counter indicate pooling across age strata when presenting results. Additional potential predictors will include variables such as: CD4 count or percentage at baseline, viral load at baseline, HAI titers to the seasonal influenza vaccine, ARV treatment, and timing of seasonal influenza vaccine. Additional predictors may be explored as additional data concerning the H1N1 virus and the study vaccine become available.

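### Section 8.1 says site differences in virus exposure may affect response, but the section 8.62 models do not commit to adjusting for site or baseline H1N1 titer, so the age test that decides on pooling may reject too often if age mix differs by site

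*Combined protocol and SAP*

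**What the plan says.** The Schema calls the trial a "Multi-center, Phase II, open label study". That establishes only that there are several sites; the substance is in section 8.

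- **Section 8.1** names two influences on response besides age. One is immune status at first immunization. The other is "differences in background exposure to the virus across sites participating in the study". It says that these "may have an impact on response to the vaccine".
- **Section 8.3** does not use site: "There will be no randomization. Subjects will be stratified by age (at least 40 subjects per group". The age quotas are study-wide.
- **Section 8.62** plans linear regression for log10 HAI titer if normality holds, and logistic regression for two HAI thresholds. Age stratum is a primary predictor. The list continues: "Additional potential predictors will include variables such as: CD4 count or percentage at baseline, viral load at baseline", followed by seasonal HAI titers, ARV treatment and timing of seasonal vaccine. It allows others to be explored later. Site, region and baseline H1N1 titer are not named.
- **Section 8.62** also gives the age result a consequence: "If immune response were to vary significantly across age strata, this would counter indicate pooling across age strata when presenting results".

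Elsewhere, secondary objective 1 (section 2.2) relates response to baseline antibody titer. Section 3.0 and Appendix IA (footnote 14) provide for H1N1 HAI at baseline. Exclusion 4.23 removes known prior H1N1 infection.

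**The concern.** Of the two influences named in section 8.1, immune status reaches the model list through CD4 and viral load. Site exposure does not reach it, either directly or through the baseline H1N1 titer.

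The trial has one arm and no randomization, and nothing balances age within site. If some sites enrol mainly younger subjects and others mainly older ones, and sites differ in response, part of the site difference will appear as an age difference. A model that treats subjects as independent will then understate the standard error for age. The consequence would be a reported age effect that is not there, and results split by stratum without need.

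The CD4, viral load and ARV effects (secondary objectives 3 and 6) could be touched in the same way. Appendix IA (footnotes 10 and 11) lets CD4 and HIV-1 RNA be run at each site's own laboratory, so those predictors may also carry site-level measurement differences. This remains a possibility, not a measured effect.

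**Working it through.** **Inputs from the documents.** Evaluable subjects: 120 (section 8.4: "This sample size is expected to yield at least 120 evaluable"). Three age groups of at least 40 (section 8.3). Primary immunogenicity results "will be reported in terms of 90% CIs around the sample proportions" (section 8.612).

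**Inputs assumed, because the documents do not give them.** Number of sites, 12 to 30. Intra-site correlation ρ, 0.05 to 0.10. Share of each site's subjects assigned to one dominant age group, 0%, 50% or 80%, with the rest random. Age test at a nominal 5%.

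**1. The plan's own figure.** The exact 90% interval for 90/120 is 67.65% to 81.39%, which matches the 68% and 81% in Table 3. All rows of Tables 1 to 3 reproduce on rounding, so there is no numerical error in the plan.

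**2. Effect of clustering on the primary interval.** Design effect = 1 + (m − 1)ρ, where m is subjects per site. With 20 sites, m = 120/20 = 6. At ρ = 0.10 the design effect is 1 + 5 × 0.10 = 1.5, the effective sample is 120/1.5 = 80, and the lower limit moves from 67.7% to 65.8%. Over 20 to 40 sites and ρ of 0.02 to 0.10, the lower limit runs from 67.5% to 65.8%. A beta-binomial check of the one-sided 95% bound (75% rate, 12 to 40 sites, ρ 0.02 to 0.10) gives coverage of 0.907 to 0.962. The effect is small.

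**3. The age test when site is ignored.** Log10 titer = site effect (variance share ρ) + residual (share 1 − ρ), with no true age effect. The test is a one-way F test on 2 and 117 degrees of freedom, with 6,000 runs per setting. Monte Carlo error at 5% is √(0.05 × 0.95/6000) = 0.3 points. Rejection rates (%):

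| Sites | ρ | Even age mix | 50% concentrated | 80% concentrated |
|---|---|---|---|---|
| 12 | 0.05 | 5.3 | 6.9 | 9.9 |
| 12 | 0.10 | 4.5 | 8.2 | 14.8 |
| 20 | 0.05 | 5.0 | 5.8 | 7.4 |
| 20 | 0.10 | 5.0 | 6.5 | 10.5 |
| 30 | 0.05 | 5.2 | 5.7 | 6.4 |
| 30 | 0.10 | 5.4 | 6.0 | 8.6 |

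Repeat runs over the same ranges gave 5.0 to 9.0% at 50% concentration and 6 to 17% at 80%.

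**4. The mechanism by hand for a binary outcome.** Suppose response is 85% at high-exposure sites and 65% at low-exposure sites, with no age effect and 40 subjects in each of two age groups. If 70% of one group and 30% of the other are at high-exposure sites:

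- first group: 0.7 × 0.85 + 0.3 × 0.65 = 0.79
- second group: 0.3 × 0.85 + 0.7 × 0.65 = 0.71
- odds ratio: (0.79/0.21)/(0.71/0.29) = 1.54, with about a 13% chance of p < 0.05

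With a 50/50 mix in both groups, each is 0.75 and there is no spurious difference.

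**5. What adjustment does.** In the step 3 setting, a REML random site intercept brings the age test to about 4 to 8%. The standard error is at most 16% larger, and no larger when age is balanced across sites. Site as a fixed factor gives 3.5 to 5.9%. For the binary outcome, GEE clustered on site with the default robust variance makes matters worse: 12.5 to 19.5% (12 sites), 8.2 to 12.9% (20) and 6.0 to 8.2% (30), against 3.7 to 9.3% for ordinary logistic regression without site. A random-intercept logistic model was not simulated.

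**The case against.** The strongest reply has four parts.

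- **The predictor list is open.** A reader might infer that the plan excludes site. It does not: further predictors are expressly allowed. This stands, but permission is not commitment. Deciding on site after seeing the age result is what a plan should prevent.
- **Exposure is handled more directly elsewhere.** Baseline H1N1 HAI is measured, objective 1 uses it, known prior infection is excluded by 4.23, and documented infection between doses excludes the subject from Step II by 4.412. This stands in part. Section 8.62 names only seasonal titers, untested infection escapes 4.23, and a baseline titer cannot reflect exposure after Dose #1.
- **The harm depends on unstated facts.** With an even age mix there is no inflation, and the highest rates need few sites and 80% concentration. This stands, and it limits the claim.
- **The consequences are limited.** The models are secondary, and section 1.22 concedes insufficient power to compare age groups. Wrongly declining to pool costs precision: by Table 3, a 75% rate has a lower limit of 61% at N = 40 against 68% at N = 120. This also stands, although a false age effect would still be reported as a finding.

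**Conclusion.** The point holds in a conditional form. Section 8.1 raises site exposure as an influence on response, and section 8.62 does not say how it will be handled. If age mix differs by site, the age test behind the pooling statement can exceed its nominal 5%: about 6 to 9% with moderate concentration, and up to about 15 to 17% in the extreme case. These sizes rest on assumed site numbers, intra-site correlation and age concentration. With an even age mix the rate is about 5%.

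Three stronger readings are tempting and not supported.

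- A reader might infer that the primary results are compromised. The response proportions and exact intervals do not rest on these models, and clustering changes them little.
- A reader might infer that the CD4, viral load or ARV effects are biased. The route is plausible, but no size has been worked out.
- A reader might infer a much larger error. A logistic simulation with 30 sites, a site SD of 1.0 on the logit scale and a 0.9 correlation between age mix and site response gave 34%. That SD implies a latent correlation of 1/(1 + 3.29) = 0.23, well above the 0.05 to 0.10 used here, and nothing in the documents supports either value.

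**What to change.** In section 8.62:

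1. Name baseline H1N1 HAI titer as a covariate in all response models.
2. Add site as a random intercept in the log10 HAI regression.
3. For the binary HAI outcomes, use random-intercept logistic regression, pooling small sites by region. Pre-specify fixed region effects as the fallback if the model does not converge; convergence warnings were common when random-intercept models were fitted to simulated data of this size.
4. Do not use GEE clustered on site unless a small-sample variance correction is specified.
5. Report the age, CD4, viral load and ARV effects with and without site, and base the pooling statement on the site-adjusted model.

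The change is to plan text only. Site is known and baseline H1N1 HAI is already scheduled for every subject, so no new data are needed. The statistical cost is a modestly wider interval for the age effect where age and site overlap, with a standard error up to about 16% larger in the extreme simulated case.
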